#### **9.6.2. Description of comparator**

Care as usual. Participants in the comparator control group will receive care as usual which includes, but not limited to, advice for healthy eating and weight loss by their doctor. This will allow for a comparison of the study intervention to the existing standard of care.

#### **9.6.3. Description of study procedure(s)**

##### Demographic questionnaire (5 mins)

Basic demographic characteristics, such as age, ethnicity, marital status, living arrangement, and smoking, will be captured using standardised questions.

##### Blood sample collection (15 mins)

About 10mL of blood will be drawn in each assessment. Samples will be sent to NHS labs for immediate analysis of ALT, AST, ALP, ELF, total and conjugated bilirubin, full blood count, INR, PT, U&E, and HbA1c.

##### Weight and body composition (3 min)

Weight will be measured with light clothing to the nearest 0.1kg using a calibrated digital scale which will also estimate body composition using bioelectrical impedance.

##### Height (2 min)

Height without shoes will be measured to the nearest 0.1cm using a stadiometer.

##### Physical examination (15 min)

Patients will have a physical examination. This may include but is not limited to an examination of the body of a participant for any possible signs or symptoms of medical conditions, such as examination for scleral icterus and pedal oedema, auscultation of the heart and lungs, and general physical findings (e.g., hepatosplenomegaly, peripheral manifestations of liver disease, ascites, wasting, or fetor). During the follow-up visits, this may also include discussion and examination to establish the presence of AEs participants might experience.

##### Concomitant medication (5 min)

Concomitant medication will be recorded.

##### Blood pressure (10 mins)

Blood pressure will be measured using a standardised protocol. The participant will sit for 5 minutes before commencing the measurements. Three measurements will be taken at one-minute intervals. The mean of the last two measurements will be used for analysis.

#### Alcohol intake questions (5 mins)

Number of units of alcohol over the previous week will be estimated based on an interview on frequency and intensity of alcohol intake.

#### Objective physical performance test (20 mins)

Low scores in the modified physical performance test are associated with obesity and the test is responsive to weight loss interventions, with high test-retest reliability. The total score is based on evaluation of nine daily activities. Each activity is scored between 0-4 following protocolised procedures; a total score of 36 indicates the highest performance. The activities are

- i. walking ~15 m
- ii. putting on and removing a coat
- iii. picking up a penny placed 30 cm in front of the participant's dominant foot
- iv. standing up from a ~40cm chair
- v. lifting a ~3 kg book from a table to a shelf ~ 30cm above shoulder height
- vi. climbing one flight of 10 stairs
- vii. performing a progressive Romberg test with feet side-by-side, semi-tandem, and full-tandem for a maximum of 10 seconds.
- viii. climbing up and down four flights of 10 stairs
- ix. performing a 360-degree turn.

Participants will also perform a hand-grip strength test in triplicate. Using their dominant hand, they will be instructed to squeeze with their maximum strength and hold steadily for a few seconds a standard hand-grip dynamometer. The grip strength measurements will be combined with the above chair stands, Romberg test, and sex to calculate the Liver Frailty Index.

#### Transient elastography (15min)

Transient elastography (Fibroscan®) will be performed by a trained assessor to measure the continuous attenuation parameter (CAP) and liver stiffness. CAP and liver stiffness will provide an indication of liver steatosis and fibrosis, respectively. Participants will be assessed using the appropriate probe.

#### Liver MRI and MRE (approximately 45 mins of scanning time)

The study MR protocol does not require contrast or injected drugs. The reproducible iron-corrected T1 relaxation time (cT1) MRI sequence will provide information on liver inflammation and fibrosis by assessing the extracellular fluid component. Liver fat will be quantified with proton density fat fraction (PDFF), which is an accurate, reproducible, and highly precise non-invasive biomarker of liver steatosis.

Once contraindications to MRI are excluded by use of the facility's screening forms, the risks of undergoing a scan are minimal. A trained scanner operator or radiographer will go through a list of possible risks with the participant before scanning. The MRI scanner consists of a large powerful magnet. Magnetic resonance imaging uses no ionising radiation. There are, however, potential hazards associated with MRI and the scanning of participants including the presence of surgical implants, participants' clothing, jewellery (such as body piercings) bodily habitus, or medical conditions. A comprehensive list of potential risks has been compiled, and the participant will be checked against this by the operator, prior to entering the controlled areas of the MRI scanners. During the actual scanning procedure, the scanner produces loud banging noises and the participant will be given suitable hearing protection (earplugs) and the ear protection will be fitted correctly. During the experiment, the participant will be able to

communicate with the operator in the control room. In addition, they will be given a call button, which allows them to alert the operator at any time. People with a history of claustrophobia may be excluded from participation in the study. All participants will still be introduced carefully to the scanner and allowed to leave at any stage, should they wish to do so. Once in the scanner, participants will be able to indicate immediately if they wish the scanning to cease by pressing a call button in their hands.

The MRE scan will be performed immediately following the MRI scan, thereby extending the scanning time by approximately 15min. Where MRE will be performed, a plastic disc-like vibration source will be placed against the body wall over the region of the liver. This transmits low-frequency vibrations through the liver. This is generally well tolerated by patients and carries no additional risks or contraindications compared with MRI. The MRE scan will be performed only at sites that have the relevant MRE infrastructure.

#### Feedback questionnaire (5 min)

Participants will be given a study-specific version of a feedback questionnaire (adapted from a previous study) on various aspects of the trial and of the intervention (for participants in the intervention group) to complete at home and return in a pre-paid envelope by post.

### **9.7. Baseline Assessments**

The baseline assessment (week 0) will last approximately 2 hours and include the demographic questionnaire, blood sample (if screening blood sample >28 days old), weight and body composition, height, physical examination, concomitant medication, blood pressure, alcohol intake questions, objective physical performance test, transient elastography, and liver MRI and MRE (where applicable).

### **9.8. Subsequent Visits**

The study schedule is available in Appendix B. The window periods will be:

- 7 days for the 2-week visit (3 days before the time the visit is expected to occur to 3 days after that)
- 2 weeks for the 4-week visit (one week before the time the visit is expected to occur to one week after that)
- 4 weeks for the 16-week visit (two weeks before the time the visit is expected to occur to two weeks after that)
- 6 weeks for the 24-week visit (three weeks before the time the visit is expected to occur to three weeks after that)

All efforts will be made for the participants to complete their visits within the above specified windows. In case of exceptional circumstances that may lead to participants having their assessments outside these window periods, we will run a sensitivity analysis to take this into account.

#### Follow-up visit 1 at 2 weeks ( $\pm$ 3 days) (~30min)

The first follow-up study visit will include a blood test and assessment of AEs (in line with section 10).

#### Follow-up visit 2 at 4 weeks ( $\pm$ 1 week) (~1h)

The second follow-up study visit will include the same assessments as the baseline visit with the addition of AEs but excluding the demographic questionnaire, height, transient elastography, liver MRI, MRE (where applicable), and HbA1c analysis.

#### Follow-up visit 3 at 16 weeks ( $\pm$ 2 weeks) (~3h)

The third follow-up study visit will include the same assessments as the baseline visit with the addition of AEs but with the exception of the demographic questionnaire and height.

#### Follow-up visit 4 at 24 weeks ( $\pm$ 3 weeks) (~3h)

The fourth follow-up study visit will include the same assessments as the follow-up visit 2 plus the feedback questionnaire.

#### Ad-hoc visits

Ad-hoc visits might take place based on the study clinician's judgement in case of an AE and in line with sections 9.9, 10, and 13.3.2.

#### Long-term follow-up through the hospital medical records

We will extract relevant data collected as part of routine care at OUH, LUH, and PHU as applicable for 2 years after each participant completes the study. The type and timing of relevant data collected will depend on data availability based on each participant's routine clinical care. This is likely to include weight, laboratory results, and health status.

## **9.9. Sample Handling**

### **9.9.1 Sample handling for study purposes**

A 10 ml (about 2 teaspoons) blood sample (~3ml for Barricor tube, ~4ml for EDTA tube, and ~2.5ml for sodium citrate tube) will be taken by a phlebotomist for examining eligibility (screening sample) and study outcomes (sample at baseline and follow-up 1-3 visits). Blood samples will be handled, analysed, and then disposed of locally at OUH, LUH, and PHU as applicable according to standard NHS procedures.

## **9.10. Early Discontinuation/Withdrawal of Participants**

During the course of the study a participant may choose to withdraw early from the study treatment at any time. This may happen for several reasons, including but not limited to:

- The occurrence of what the participant perceives as an intolerable AE.
- Inability to comply with study procedures
- Participant decision

Participants in the care as usual group: They may opt out of study assessments but may remain on study follow-up.

Participants in the intervention group: They may stop the intervention and/or study assessments but may remain on study follow-up and will be encouraged to do so. However, if they choose not to attend the 2-week or 4-week safety assessment, they will not be able to continue the intervention but can remain on study follow-up. The visits should be completed within the specified window (as per section 9.8) but provisions will be made on a case-by-case basis to have this assessment completed outside this window in exceptional circumstances (e.g. if the patient is self-isolating due to COVID-19 but is keen to get assessed and resume the intervention).

All participants may also withdraw their consent, meaning that they wish to withdraw from the study completely. In the case of withdrawal from both treatment (intervention) and active follow up, the following options for a tiered withdrawal from the study will be given to participants and explained in the participant information sheet. According to the design of the trial, participants may have the following three options for withdrawal;

- 1) Participants may withdraw from active follow-up and further communication but allow the trial team to continue to access their medical records and any relevant hospital data that is recorded as part of routine standard of care; i.e., imaging scans, blood results, and disease progression data, etc.
- 2) Participants can withdraw from the study but permit data and samples obtained up until the point of withdrawal to be retained for use in the study analysis. No further data or samples would be collected after withdrawal.

In addition, the Investigator may discontinue a participant from the intervention at any time if the Investigator considers it necessary for any reason including, but not limited to:

- Pregnancy
- Ineligibility (either arising during the trial or retrospectively having been overlooked at screening)
- Significant protocol deviation
- Significant non-adherence with treatment regimen or trial requirements
- An adverse event which requires discontinuation of the trial intervention or results in inability to continue to comply with trial procedures
- Disease progression which requires discontinuation of the trial intervention or results in inability to continue to comply with trial procedures
- Criteria of the algorithm in Appendix E are met.
- If enhanced observation is necessary as per section 10 but is not possible

The follow-up of participants that have withdrawn from the intervention but not from active follow-up will continue with the standard follow-up assessments of the study.

If the intervention is discontinued due to criteria in Appendix E, the intervention may be re-introduced with approval of the Trial Steering, Data Monitoring, and Ethics Committee (TSDMEC) if another cause of the elevation is identified. If on re-introduction, the elevations in liver function tests persist, the intervention must be discontinued and enhanced observation must continue as per section 10. Data from randomised participants will be analysed and post-randomisation withdrawal from the study will not result in exclusion of the data for that participant from the analysis. If the participant is withdrawn before randomisation, they will be replaced (as per section 9.3). The type of withdrawal and reason for withdrawal will be recorded in the CRF. If the participant is withdrawn due to an AE, the Investigator will arrange for frequent telephone calls as agreed with the participant (or an ad-hoc study visit upon the study clinician's judgement) until the AE has resolved or stabilised (also see sections 9.7, 10, and 13.3.2). If a participant is withdrawn from treatment due to pregnancy the pregnancy will be followed-up to outcome. See the Safety Reporting section below.

### **9.11. Definition of End of Study**

The end of trial is the point at which all the data has been entered and queries resolved.

## **10. SAFETY REPORTING**

Potential AEs will be recorded at each follow-up assessment. Participants may contact the research team (e.g., over the phone) at any time point during the course of the study to report potential AEs. AEs will be recorded as part of the CRF of the subsequent study visit (e.g., an AE occurring between weeks 4 and 16 will be recorded as part of the 16-week assessment).

One previous trial reported no SAEs due to the TDR, whereas another reported two SAEs potentially related to the TDR in the same participant. There was evidence that for every five people one would experience an adverse, mostly mild, event because of the TDR programme. Constipation, headache, fatigue, and dizziness are the most common AEs albeit occurring in a minority of participants (<8% each) and disappeared over time. Less common side effects include dry mouth, abdominal pain, bad breath, diarrhoea, hair loss, dry skin, mood changes, and feeling cold.

The safety reporting window begins from the first day of the intervention for participants in the intervention group and from the day of randomisation for participants in the control group. It finishes for both groups when the participant completes the study. The limit of investigator follow-up of SAEs will be until the participant completes the study. This requirement will be the same for all SAEs.

Laboratory abnormalities without clinical significance are not recorded as AEs or SAEs. However, laboratory abnormalities that require enhanced observation, medical or surgical intervention, or lead to discontinuation of the intervention must be recorded as an AE, as well as an SAE, if applicable.

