### **Enhanced observation**

Some patients with CC-NAFLD may have elevated liver function tests at baseline. Participant will enter into enhanced observation as per the algorithm in Appendix D. Enhanced observation will include:

- Repeating a blood test to assess ALT, ALP, total bilirubin, INR within 5 days of results.
- Obtaining a more detailed history of symptoms and prior or concurrent disease.
- Obtaining a history of concomitant drug use (including non-prescription medications and herbal and dietary supplement preparations), alcohol use, recreational drug use, adherence to the dietary intervention (including consumption of regular foods).
- Obtaining a history of exposure to environmental chemical agents.
- Ruling out other causes of liver disease as needed (obtain viral hepatitis panel, imaging for evaluation of biliary tract disease, etc, if required in the opinion of a medically qualified investigator).
- Continue to monitor the above tests weekly until the tests have fallen below the triggering threshold and then monthly for 2 months, and then as per protocol and until the end of the 24-week follow-up.

During enhanced observation, the intervention can be continued, if desired and results do not trigger intervention discontinuation (Appendix E), at the discretion of a medically qualified investigator.

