### 13.3.2 Trial Steering, Data Monitoring, and Ethics Committee (TSDMEC)

As this is an unblinded trial, the Trial Steering Committee and the Data Monitoring and Ethics Committee will be combined. The TSDMEC of 3 independent members [chair (hepatologist), academic with expertise in clinical trials, clinician] will review and meet online to approve the protocol and meet thereafter every 6 months or following completion of the 4-week follow-up of 8 randomised participants (whichever is earlier) to review data quality and monitor ethics and safety based on unblinded data and advise the TMG. The TSDMEC may meet more frequently and request to review specific analyses (e.g. comparing rates of AEs by trial group or other subgroup) at their discretion and as needed. They will review an extra safety profile report between the scheduled meetings of biochemistry and relevant data of participants discontinuing the intervention or being on enhanced observation. They will review SAEs as they occur. They will formally recommend at the end of each meeting whether the trial should continue with no changes, continue with protocol modifications, or be stopped. Its role, constitution, and composition will follow NIHR guidelines.

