### Abbreviations:

ALT: Alanine transaminase

AST: Aspartate transaminase

ULN: Upper limit of normal

TB: Total bilirubin

Signs or symptoms of hepatic decompensation: jaundice, ascites, hepatic encephalopathy, or variceal haemorrhage.

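### One of the three triggers that make a laboratory abnormality a mandatory adverse event can be met only in the intervention arm

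*Protocol*

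**What the plan says.** Protocol section 10 (Safety Reporting) sets a default and an exception. The default is "Laboratory abnormalities without clinical significance are not recorded as AEs or SAEs". The exception is that "laboratory abnormalities that require enhanced observation, medical or surgical intervention, or lead to discontinuation of the intervention must be recorded as an AE", and as an SAE where that applies. The exception has three alternative triggers: enhanced observation, medical or surgical treatment, and stopping the intervention.

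Three other places bear on it:

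- **Enhanced observation (section 10).** "Participant will enter into enhanced observation as per the algorithm in Appendix D". The sentence does not name an arm.
- **Discontinuation (section 9.10).** Meeting the Appendix E criteria is one listed reason for stopping. More generally, "the Investigator may discontinue a participant from the intervention at any time if the Investigator considers it necessary for any reason".
- **Committee (section 13.3.2).** Between meetings the TSDMEC receives an extra safety report on "biochemistry and relevant data of participants discontinuing the intervention or being on enhanced observation". It may also ask for AE rates by trial group.

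The comparator is care as usual (section 9.6.2). Participants and clinicians are not blinded (section 9.5).

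**The concern.** The third trigger classifies an abnormality by what was done about it, and that action exists in one arm only. Because the triggers are alternatives, it changes the record only when the first two are not met. Its whole added effect is therefore extra mandatory AEs among participants on the diet, after a decision taken by people who know the allocation.

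Adverse events are a secondary outcome (section 6), and section 10 defines a reporting window for controls, so control AEs are meant to be collected. The committee recommends early termination on its review of AEs and SAEs (section 11.6) and adjudicates the safety criterion for progression to a full trial (section 11.10). With 16 and 8 participants per arm, one extra participant with an AE moves the intervention rate by 1/16 = 6.25 percentage points. Some background laboratory worsening is to be expected in cirrhosis, so the two arms should be counted by the same rule.

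**Working it through.** The plan states no figure on this point, so there is none to reproduce. The check traces the rule through each arm, then shows how the size depends on one unknown.

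**1. The triggers by arm**

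| Trigger in section 10 | Intervention | Control |
|---|---|---|
| Enhanced observation | possible | possible (no arm restriction in the text) |
| Medical or surgical treatment | possible | possible |
| Stopping the intervention | possible | impossible (care as usual) |

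**2. When the third trigger acts alone.** Section 10 presents discontinuation as something that results may trigger while a participant is already under enhanced observation. Section 9.10 says that, if elevations persist after the diet is re-introduced, "the intervention must be discontinued and enhanced observation must continue as per section 10". For liver tests the first and third triggers therefore overlap, probably heavily. Two routes remain outside the overlap:

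- a discretionary stop under section 9.10, which need not meet any Appendix D threshold;
- a non-liver result. The trial bloods include full blood count, U&E and HbA1c (section 9.6.3, Appendix B), while the repeat test under enhanced observation covers ALT, ALP, total bilirubin and INR. A U&E result that led to stopping the diet would be a mandatory AE. The same result in an untreated control would have no mandatory route.

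**3. Illustration of size.** Inputs: 16 intervention and 8 control participants (section 11.3). Two quantities are assumed because the protocol gives neither:

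- p, the proportion with an abnormality that would be reportable in the diet arm, set equal in both arms;
- q, the share of these caught only by the third trigger.

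Expected AE records are 16p in the intervention arm and 8p(1 − q) in controls. The spurious risk difference is p − p(1 − q) = pq.

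| p | q | Intervention (of 16) | Control (of 8) | Spurious difference |
|---|---|---|---|---|
| 10% | 0 | 1.6 | 0.8 | 0 |
| 10% | 25% | 1.6 | 0.6 | 2.5 points |
| 10% | 50% | 1.6 | 0.4 | 5 points |
| 20% | 0 | 3.2 | 1.6 | 0 |
| 20% | 25% | 3.2 | 1.2 | 5 points |
| 20% | 50% | 3.2 | 0.8 | 10 points |
| 20% | 100% | 3.2 | 0 | 20 points |

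The rows with q = 100% and q = 0 are bounds. The text rules out neither p nor q, but the overlap in step 2 argues against values of q near 100%.

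**4. Exposure of the numerical stopping guide.** Section 11.6 requires no control SAEs and a Wilson lower 95% bound of at least 30% for intervention SAEs. With x events in n participants, p̂ = x/n and z = 1.96, the lower bound is

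[p̂ + z²/(2n) − z√(p̂(1 − p̂)/n + z²/(4n²))] / (1 + z²/n).

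- 8 of 16: (0.5000 + 0.1200 − 0.2728)/1.2401 = 28.0%, below the cut-off.
- 9 of 16: (0.5625 + 0.1200 − 0.2711)/1.2401 = 33.2%, at or above the cut-off.

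At an earlier review the count is smaller (5 of 8 gives 30.6%) but still a majority of participants. The guide counts SAEs, and the SAE definitions in section 10.1 do not depend on arm.

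**5. Exposure of the co-primary safety outcome.** It rests on criteria for severe change in ALT, AST and total bilirubin at weeks 0, 2, 4, 16 and 24 (section 6). Both arms have these tests on the same schedule (Appendix B), so AE recording does not enter into it.

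**The case against.** The strongest objection is that two of the three triggers are neutral between arms, and that a control with the same liver result enters enhanced observation and is recorded that way. This stands. A reader might infer that an identical result generally counts in one arm and not in the other. The text does not support that, because it would need nearly every case to be caught by discontinuation alone.

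A reader might also point to bilirubin. The abbreviation key to Appendix E includes "TB: Total bilirubin", while the key to Appendix D lists only ALT, AST and ULN, which could suggest that a bilirubin-only rise leads to stopping but not to enhanced observation. That inference is not safe. A key lists abbreviations and not criteria, the figures themselves are not available here, and section 10 includes total bilirubin among the tests to be followed until they fall below the triggering threshold.

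Three further points have weight:

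- The rule is a floor. Section 10 exempts only abnormalities without clinical significance, so an investigator may still record a significant result in a control. That is true, but recording is then optional in one arm and compulsory in the other.
- Laboratory worsening in controls stays visible through the co-primary outcome, and section 11.2 reports the percentage worsening in each liver outcome. This stands for liver tests.
- Section 11.4 restricts the AE analysis to participants commencing the intervention, so the planned analysis may make no comparison by arm. That is a separate problem. It does not remove this one, because the committee may still compare AE rates by group.

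Finally, the committee's extra report is only partly selected by the arm-specific action, since participants under enhanced observation are included whichever arm they are in.

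**Conclusion.** The point holds in a limited form. One of three triggers depends on the arm, and its only added effect is more mandatory AEs on the diet. It bears on abnormalities that lead to stopping the diet without enhanced observation or treatment: discretionary stops, and possibly non-liver results. How many there would be cannot be determined without the Appendix D and E figures. The spurious difference is zero under full overlap and 2.5 to 10 points for p of 10% to 20% and q of 25% to 50%, all of them assumed values.

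By-arm AE counts and the committee's judgement are exposed. The co-primary biochemistry outcome is not. The SAE cut-off hardly is, since it needs 9 of 16 intervention SAEs at full enrolment. It would go too far to say that the rule hides control-arm liver worsening or would by itself drive the trial to stop. This is a small ascertainment asymmetry, worth removing because safety signals are a co-primary objective and the change is nearly free.

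**What to change.** Keep the three existing triggers in section 10 and make these additions:

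1. State that *any laboratory result meeting the Appendix D or Appendix E laboratory criteria is recorded as an AE in either arm, whether or not the intervention is stopped*.
2. Record discontinuation on the AE form as an action taken, and flag AEs recorded solely because of discontinuation, so that by-arm comparisons can be shown with and without them. The flag deals with discretionary stops and non-liver results, which no threshold in the appendices may cover.
3. Give the TSDMEC the same threshold-based laboratory listing for both arms alongside its report under section 13.3.2.

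The result-based criterion should be added to the triggers and not replace them. Replacing them would drop abnormalities that were treated, or that prompted a stop below threshold, and so lose safety information. The discontinuation rule itself stays as it is.

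The cost is wording, one extra field on the form and a few more control AEs to record. No extra blood tests are needed, because both arms already have the liver panel, full blood count and U&E at weeks 2, 4, 16 and 24.
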